## 2. Materials and Methods

The SPIRIT 2013 Checklist has been used to assure the quality of the protocol [35]. This protocol has been registered in trials.gov with the number NCT04815486.

### 2.1. Study Design and Participants

Participants will be recruited in the Brain Injury Unit or Rehabilitation Unit of the Beata María Ana Hospital; patients referred from other centres and self-referred patients will also be considered. The subjects included will be assessed by a neurologist ([name]) and a physiotherapist ([name]). All patients will have had a hemispheric ischemic or hemorrhagic stroke (>3 months after stroke) diagnosed in at least one brain-imaging test and presenting motor sequelae in the upper limb. We have ruled out the first three months since the phenomenon is known as “spontaneous recovery” [36] takes place in time, and therefore, it would be difficult to discern the cause of the clinical improvement that we expect from patients. The patients included in the study will have an alteration of mobility and/or functionality in the upper limb related to the stroke and with a score equal to or greater than 25 according to the Fugl-Meyer Assessment for upper extremity (FMA-UE) [37]. The rest of the specific inclusion and exclusion criteria are shown in Table 1.

The study design corresponds to a randomized, single-blind, controlled clinical trial in which patients are randomly assigned to two groups: 1. Conventional rehabilitation + bilateral rTMS + Immersive multimodal BCI-VR training system NeuRow (NeuroRehabLab, Funchal, Portugal), and 2. Conventional rehabilitation + bilateral rTMS.

Regarding adherence strategies, sessions missed up to the established limit will be restored the following week. Flexible therapy schedules will also be offered, and patients’ families will be contacted directly by phone to confirm evaluation dates, thus reinforcing treatment adherence [38].

To calculate the sample size, the GRANMO calculator was used *(Sample size and power calculator (v. 7.12.), Institut Municipal d’Investigació Mèdica, Barcelona, Spain)*. Accepting an alpha risk of 0.005 and a beta risk of 0.2 in a one-sided contrast, 23 subjects are required to detect a difference equal to 4.9 points, the minimal clinically important difference of the Fugl-Meyer assessment scores for wrist/hand [39]. Considering a 15% loss, it will be necessary to reach a sample of 21 patients in each group.

Randomization and blinding will be made using the application Research Randomizer (Social Psychology Network, Middletown, CT, USA) [40] to form the groups. A code consisting of two digits (1 and 2) will be used. The application offers a random list of 30 numbers with digits 1 and 2. This sequence will be carried out remotely by a blind researcher who is not involved in other investigation procedures. After the randomization process, another blind staff member will assign patients among groups. The allocation concealment will be made with closed, sealed, and sequentially numbered envelopes. The evaluators will receive the patients in a different room, ignoring which group they belong to.

To assess the adverse effects, participants will be asked at the end of each session if they experienced effects such as tingling, burning, headache, and drowsiness, among others and the intensity of this sensation. Guidelines for safety on rTMS protocols will be followed [41]. However, no severe adverse effects are expected. Any adverse effect will be notified to a licensed medical doctor. Management of possible adverse effects will be individualized and according to the severity.

Regarding data processing security, data will be recorded separately and will be anonymized and guarded following current European data protection laws. All data will be recorded and verified twice in a database specifically designed for the studies.

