## 1. Introduction

Stroke is a leading cause of long-term disability; it reduces mobility in more than half of stroke survivors age 65 and over [1].

Despite the lack of objective prognostic factors regarding the patient’s functionality after a stroke, we know that age, the level of initial disability, and the location and size of the lesion are elements that affect the evolution of post-stroke rehabilitation [2].

After a stroke, the recovery of lost functions in the brain is achieved thanks to reorganizing networks in a process known as plasticity. Some damaged brain tissues may recover, or undamaged areas may take over some functions.

One of the most relevant aspects of the rehabilitation prognosis is the time of evolution. After a stroke, improvement is noticeably reduced over the second month, finding stabilization around the sixth month. One of the reasons that explain this fact is the reduction of neuroplasticity [3]. There are indicative studies that reflect that, six months after a stroke, more than 60% of subjects will have a non-functional hand for Basic Activities of Daily Living (BADL), and 20–25% will not be able to walk without assistance [4]. These impairments determine the important global burden that stroke represents [5]. It is relevant to emphasize that the degree of disability after the rehabilitation process will be determined by the combination of existing motor, sensory, and neuropsychological deficiencies [6].

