On the one hand, exogenous neuromodulation effects are produced mainly by changes directly induced in cortical excitability [19], and on the other hand, endogenous neuromodulation is believed to have more widespread subcortical effects [20,21]. Currently, the exact mechanisms underlying motor recovery using neuromodulation techniques are still being investigated. Simultaneous activation of inputs and outputs to cortical motor areas is believed to trigger Hebbian plasticity, which strengthens cortical-subcortical connectivity. Improvements in this cortical-subcortical connectivity have been linked to better motor recovery after stroke [22,23].

One of the probable causes of the short-term effects of these techniques is the ceiling effect of changes in cortical excitability that can be achieved non-invasively, but despite the good results achieved with the use of non-invasive neuromodulation techniques individually, there is a shortage of validated neurorehabilitation protocols that integrate different approaches that have been proven to be effective individually.

It has been suggested rTMS may be a good conditioning method whose effect would be to increase brain plasticity that would improve the results of subsequent rehabilitation [24]. There are already several studies that compare rTMS alone with its combination with motor rehabilitation showing good results when rTMS is used as a primer that may help to reach a greater cortical activation and boosting plasticity [8,25,26,27]. Motor imagery and action observation have been shown to effectively activate the same brain areas as an actual movement [28]; up to date, it has not been combined with rTMS.

There is increasing evidence of Brain–Computer Interfacing (BCI) efficacy as rehabilitation technology in patients with severe motor impairments [29]. This is the case with NeuRow [30]. It is an immersive multimodal Brain–Computer Interfacing (BCI) training paradigm that combines motor imagery and embodied neurofeedback using virtual reality. NeuRow has been designed to be used by the chronic stroke patient population [31], and its efficacy has been shown in a pilot study. It shows clear improvements and recovery regarding motor function in terms of clinical scales (FMA, MAS, SIS), self-reported scales, electrophysiological data, and brain imaging data (fMRI). There is evidence that BCI-based rehabilitation promotes lasting improvements in motor function in chronic stroke patients with hemiparesis [32].

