Both approaches, the NeuRow training paradigm (NeuroRehabLab, Funchal, Portugal) and bilateral rTMS protocols, are likely to complement their effects, achieving a stronger neuroplasticity enhancement in stroke patients. Both have been used separately for the treatment of motor sequelae in the upper limbs after stroke [8,31,33]. The effects of these combined techniques are not likely to be based only on the increase of cortical excitability but also on subcortical mechanisms.

The efficacy of rTMS and motor imagery has been previously demonstrated, but their combination has not been tested yet. The main objective of this study is to carry out a double-blind, randomized, controlled trial aiming to study the clinical effect of immersive multimodal BCI-VR training using NeuRow system (NeuroRehabLab, Funchal, Portugal) after bilateral neuromodulation with rTMS compared to bilateral rTMS plus conventional rehabilitation in upper limb motor sequelae after subacute stroke (>3 months). We will look for changes in: 1. isometric strength in the upper limb; 2. functional motor scales of the upper limb; 3. hand dexterity; and 4. cortical excitability changes. Our main hypothesis is that multimodal BCI-VR training will be superior to the use of conventional motor imagery as adjuvant therapy to bilateral rTMS.

This protocol combines techniques that have proven to be cost-effective [34]. If it is shown that the clinical improvement with this combination is significant, it will open a new line of combined neuromodulation approaches to reach an effective method for the upper limb motor neurorehabilitation after a stroke.

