**Figure 2 medicina-57-00736-f002:**
[figure not shown]
Schematic representation of intervention protocol. It includes the days of the week and duration of each block of outcomes measurement in pre- and post-evaluation (FMA-UE—Fugl-Meyer Assessment for upper extremity; MI—Motricity Index; SIS—Stroke Impact Scale; RMT—Resting Motor Threshold; NHPT—Nine Hole Peg Test; FTT—Finger Tapping Task; MAS—Modified Asworth Scale; NSA—Nottingham Sensory Assessment; BI—Barthel Index; EEG—Electroencephalogram. Thursday/90–120 min; Monday/60 min; Control Intervention/Monday to Friday/10 rTMS sessions and Experimental Intervention: Monday to Friday/10 rTMS sessions and Monday, Wednesday, and Friday/12 NeuRow sessions).

**Table 1 medicina-57-00736-t001:** Inclusion and exclusion criteria.

INCLUSION CRITERIA	EXCLUSION CRITERIA
Older than 18 years old.	History of seizure or brain aneurysm
Ischemic or hemorrhagic cerebrovascular injury diagnosed by a neurologist and who have at least one brain-imaging test	Pacemakers, medication pumps, metal implants in the head (except dental implants)
Onset of hemispheric ischemic or hemorrhagic stroke >3 months	Clinical instability
Kinesthetic and Visual Imagery Questionnaire (KVIQ) >55.	Muscle tone in the wrist and hand with a modified Ashworth scale (MAS) score equal to or higher than 3 in the wrist
Stability in antispastic medication for more than 5 days	Other pre-existing neurological diseases or previous cerebrovascular accidents with sequelae
Able to read and write	Aphasia
Sufficient cognitive ability to understand and perform tasks: Token Test >11	Previous TMS after stroke Hemispatial neglect (Bells Test >6 omissions on one side) Visual problems
	Flaccid paralysis Brunnstrom’s stage = 1

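### The population is labelled subacute, but entry more than 3 months after stroke has no upper limit, and the cut-off reduces spontaneous recovery without removing it

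*Protocol article*

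**What the plan says.** The objective in Section 1 describes the target as "upper limb motor sequelae after subacute stroke (>3 months", and the abstract uses the same label. The entry rule is one-sided in both places where it appears: Section 2.1 has "All patients will have had a hemispheric ischemic or hemorrhagic stroke (>3 months after stroke" and Table 1 has "Onset of hemispheric ischemic or hemorrhagic stroke >3 months". Neither gives a latest time.

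Section 2.1 explains the bound: "We have ruled out the first three months since the phenomenon is known as “spontaneous recovery" occurs in that period, and otherwise "it would be difficult to discern the cause of the clinical improvement that we expect from patients". Section 1 counts time since stroke among the most relevant aspects of rehabilitation prognosis and describes its course: "improvement is noticeably reduced over the second month, finding stabilization around the sixth month". Section 1 also says that "NeuRow has been designed to be used by the chronic stroke patient population".

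Section 2.1 describes allocation by one random list of the digits 1 and 2 and names no strata. Section 2.4 lists t-tests (independent or paired), ANOVA and correlations, and does not mention time since stroke.

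**The concern.** Two statements do not fit the rest of the document.

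The first is the label. An entry rule open at the upper end admits a patient 4 months after stroke and a patient 5 years after stroke alike. Recruitment also takes referrals from other centres and self-referrals (Section 2.1), so long-standing cases are a realistic prospect. A result reported for subacute stroke could rest largely on chronic patients.

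The second is the rationale. It presents the 3-month bound as the answer to spontaneous recovery, whereas the Introduction places the plateau about three months later. Some patients would still be improving naturally during the trial and others would not, and nothing described in the article separates them. At stake are precision, the balance of a prognostic factor that the protocol itself stresses, and the reading of change within each arm.

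**Working it through.** The point rests on comparing passages. The document gives no figure to reproduce; the arithmetic below only shows scale.

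**1. Entry window against label.** Lower bound: more than 3 months (Section 2.1, Table 1). Upper bound: none. Label: subacute (abstract, Section 1). The label is narrower than the rule.

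**2. Cut-off against stated course of recovery.** Section 1: slowing over month 2, plateau around month 6. NeuRow training lasts four weeks (Section 2.2.2), and the abstract puts the last assessment 15 days after the final session. A patient who starts training at 3.5 months finishes at about 3.5 + (28 + 15)/30 = 4.9 months, before the stated plateau.

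**3. Chance imbalance.** Inputs: 42 patients, 21 per arm (abstract, Section 2.1). Assumption: *K* of the 42 are at 3 to 6 months. With fixed arms of 21, the number of early patients in one arm is hypergeometric(42, *K*, 21). The probability that the arms differ by 4 or more early patients (4/21 = 19 percentage points) is:

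| *K* early of 42 | P(difference of 4 or more) |
|---|---|
| 8 | 24% |
| 13 | 18% |
| 17 | 21% |
| 21 | 22% |
| 22 | 35% |

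The values jump because the difference is always even when *K* is even and odd when *K* is odd. For *K* = 13, 17 and 21, 4 or more therefore means 5 or more. If instead the counts are taken as two independent Binomial(21, *p*) variables, the probability is 28% at *p* = 0.5 and 24% at *p* = 0.3; for 5 or more it is 16% and 13%.

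**4. Shift in the arm difference.** Shift = imbalance × extra gain of early patients. Assumed extra gain over the trial: 2 to 5 Fugl-Meyer points.
- 0.19 × 2 = 0.4 points
- 0.24 × 5 = 1.2 points

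Against the 4.9-point target (Section 2.1) this is 0.4/4.9 = 8% to 1.2/4.9 = 24%. The typical shift is smaller: with *K* = 21 the imbalance has a standard deviation of 0.156, so a 2-point gain gives 0.156 × 2 = 0.31 points.

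**5. Added variance.** Mixing adds *p*(1 − *p*)*g*² to the outcome variance, where *g* is the extra gain. At *p* = 0.5 and *g* = 2 this is 0.25 × 4 = 1.0, or 4% of 25 (assumed SD 5). With 18 completers per arm (about 21 less 15%), the stated one-sided alpha of 0.005 and an assumed SD of 5 to 6, power falls by about 1 to 2 percentage points at *g* = 2 and by about 9 to 16 points at *g* = 6.

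**6. Would separate lists cure the imbalance?** Simulating simple, unblocked randomisation within each stratum, with 21 early patients of 42, gives a 28% chance of a 19-point or larger imbalance; with 13 early patients it is 19%. Unblocked separate lists balance no better than one unblocked list, so stratification needs blocks.

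**The case against.** The strongest reply is that the trial has a concurrent randomised control arm and its main hypothesis is between arms. Natural recovery is then expected equally on both sides, and chance imbalance is already covered by the standard error of the test. This stands. A reader might infer that the comparison is biased or invalid; the documents do not support that.

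It is also said that month 3 is a defensible cut, because Section 1 has improvement already clearly slower over month 2, and spontaneous recovery is a narrower notion than improvement in general. This stands in part. The bound removes the steepest phase, and nothing here shows the bound to be wrong. What fails is the suggestion that, past month 3, the cause of improvement is no longer in doubt.

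A reader might infer that enrolling chronic patients is itself an error. It is not: a wide window is a legitimate choice, and the remark that the device was designed for chronic stroke contradicts only the label. Nor does Section 2.4 say that paired tests will be read as efficacy. Both arms receive rTMS and conventional rehabilitation, so a pre/post gain could not isolate NeuRow even in chronic patients. Residual recovery adds a further reason for not reading it that way.

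Finally, covariates may be set in an analysis plan that is not shown, and age, initial disability and lesion features are also named as prognostic. That tempers the request for adjustment. It does not affect the label or the rationale, which this document fixes.

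**Conclusion.** The point holds as a matter of labelling, rationale and efficiency. The stated population is narrower than the entry rule, and the cut-off reduces residual recovery without removing it, by the protocol's own description. There is no systematic bias between arms.

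The size cannot be determined from the document. The range of 0.4 to 1.2 points depends on an assumed extra gain of 2 to 5 points and on an imbalance of 4 or 5 patients having occurred. The upper end is generous, since it supposes natural recovery in early patients that by itself slightly exceeds the 4.9-point target. With a small extra gain, the loss of power is slight. The mismatch in the text needs none of these assumptions.

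**What to change.** 1. In the abstract and the objective, describe the population as stroke more than 3 months after onset, subacute and chronic. Report the numbers at 6 months or less and over 6 months in each arm.
2. Prespecify time since stroke as a term in the between-arm comparison, either split at 6 months (the protocol's own plateau) or continuous, unless the analysis plan already does so. If the allocation list can still be changed, stratify on it with blocked lists.
3. Amend the rationale in Section 2.1 to say that the cut-off reduces but does not remove spontaneous recovery, so that efficacy is judged only between arms.

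The cost is some rewording, one degree of freedom and, if stratification is adopted, a little more work for whoever prepares the lists. Time since stroke is already needed for eligibility, so no extra patients or procedures are required. If recruitment has begun, the relabelling, the reporting by stratum and the adjustment remain available.

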### 2.4. Data Analysis

Parametric tests will be used for the analysis of the results if compliance with the assumptions (normality and equality of variance) and the sample size allow it. These analyses include a Student’s *t*-test for independent or paired samples, ANOVA of one or two factors and repeated measures, and Pearson correlations.

Due to the data nature, analyses will be completed with nonparametric tests such as χ2 and Wilcoxon. The residual effect, period effect, and sequence effect checks will be made.

In all analyses, a confidence level of 0.95 will be adopted. The data analysis will be carried out with the help of the statistical program SPSS 25.0 (SPSS Inc., Chicago, IL, USA).

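### The sample-size statement contradicts itself and the analysis section: 23 subjects with 15% loss does not give 21 per group, and the design alpha (0.005 one-sided) is not the analysis level (0.05), so the stated 80% power is unsupported

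*Protocol article*

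**What the plan says.** The sample-size paragraph in section 2.1 of the protocol article opens: "Accepting an alpha risk of 0.005 and a beta risk of 0.2 in a one-sided contrast". It continues: "23 subjects are required to detect a difference equal to 4.9 points". The difference is described as "the minimal clinically important difference of the Fugl-Meyer assessment scores for wrist/hand". The allowance for losses follows: "Considering a 15% loss, it will be necessary to reach a sample of 21 patients in each group". The Abstract gives 42 participants in total, which agrees with two groups of 21.

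The paragraph does not say whether 23 is per group or the total, and it gives no standard deviation.

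Section 2.4 states: "In all analyses, a confidence level of 0.95 will be adopted". It does not say whether tests are one- or two-sided.

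**The concern.** An allowance for losses can only raise a sample size. If 23 is per group, the number falls to 21 after the allowance. If 23 is the total, it rises to 42, far more than 15% loss calls for. The final number therefore does not follow from the figures beside it.

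The design and the analysis also use different error rates. One-sided 0.005 corresponds to a two-sided 99% interval, whereas the analysis section works at 95%.

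Sample size, alpha and power show whether the trial can detect the difference it names. As written, a reader cannot tell which alpha governs the conclusion. Nor can the reader tell whether 42 participants is too few, about right or more than needed.

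**Working it through.** **Inputs.** From section 2.1: alpha 0.005 one-sided, beta 0.2, difference 4.9 points, 23 subjects before loss, 15% loss, 21 per group. From the Abstract: 42 in total. From section 2.4: confidence level 0.95. The SD is not given.

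**Step 1: the plan's own figure.** The standard allowance for a loss fraction d is n/(1 − d); a common variant is n × (1 + d).

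| Reading of 23 | n/(1 − 0.15) | n × 1.15 | Stated |
|---|---|---|---|
| Per group | 27.06, so 28 per group (56 total) | 26.45, so 27 per group (54 total) | 21 per group (42 total) |
| Total | 27.06, so 28 total (14 per group) | 26.45, so 27 total | 42 total |
| Total, each group rounded up first (11.5 to 12) | 14.1, so 15 per group (30 total) | 13.8, so 14 per group (28 total) | 42 total |

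No row reproduces 21 per group or 42 in total. Going from 23 to 42 would need a loss of 1 − 23/42 = 45%. Working backwards, 21 × 0.85 = 17.85, or about 18 evaluable per group (18/0.85 = 21.2; 18 × 1.15 = 20.7). Neither 18 per group nor 36 in total appears in the text.

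This step does not involve alpha or the SD.

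**Step 2: the SD that 23 implies.** With two equal groups and the normal approximation, n per group = 2(z_α + z_β)²(SD/4.9)², so SD = 4.9 / [(z_α + z_β)√(2/n)]. Here z_β = 0.842, and z_α = 2.576 (one-sided 0.005), 1.645 (one-sided 0.05) or 1.960 (two-sided 0.05).

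| Design alpha | SD if 23 per group | SD if 23 total (11.5 per group) |
|---|---|---|
| 0.005 one-sided | 4.86 | 3.44 |
| 0.05 one-sided | 6.68 | 4.73 |
| 0.05 two-sided | 5.93 | 4.19 |

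**Step 3: power with 18 evaluable per group.** Power = Φ(4.9/(SD√(2/18)) − z_α). Since √(2/18) = 1/3, this is Φ(14.7/SD − z_α).

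Tested at the same alpha as the design:
- 23 per group: Φ(14.7/4.86 − 2.576) = 67%; Φ(14.7/6.68 − 1.645) = 71%; Φ(14.7/5.93 − 1.960) = 70%. With the t distribution used for both the SD and the power, the first is 66%. The range is about 66–71%.
- 23 in total: Φ(14.7/3.44 − 2.576) = 96%; Φ(14.7/4.73 − 1.645) = 93%; Φ(14.7/4.19 − 1.960) = 94%.

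Sized at one-sided 0.005 with 23 per group (SD 4.86), but tested at two-sided 0.05: Φ(14.7/4.86 − 1.960) = 86%. The noncentral t with the same SD gives 84%.

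**Step 4: range over assumed SDs.** The SD is an assumption here, not a figure from the documents. For SDs of 4 to 8 and 17.85 evaluable per group, power runs from 86% down to 23% at one-sided 0.005, and from 96% down to 45% at two-sided 0.05. With 18 per group, 80% power is reached for SDs up to 14.7/(z_α + z_β): 4.30 at one-sided 0.005, 5.91 at one-sided 0.05 and 5.25 at two-sided 0.05.

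**The case against.** A reader might infer that the trial is underpowered. The documents do not support that. Section 2.1 does not say that 23 is per group. If it is the total, 18 evaluable per group exceeds the requirement. The description of randomisation, also in section 2.1, mentions a list of 30 numbers, which matches the 30 that a total of 23 gives when each group is rounded up. That settles nothing, since the list also falls short of the stated 42, but it is a reason not to treat the per-group reading as the natural one.

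The alpha mismatch does not point to lost power either. A trial sized at 0.005 and tested at 0.05 gains power, and even the per-group reading then stays above 80%. Figures well below 66% can be obtained. One way is to combine an SD from the normal approximation with power from the noncentral t. Another is to assume both that 0.005 is a misprint and that the test is two-sided. The first is partly an artefact of method, and the second needs assumptions that the text does not make.

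The value 0.005 may well be a misprint for 0.05. That would bring the levels into line, leaving only the sidedness of the analysis unstated. It would not repair the step from 23 to 21.

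An article may leave the SD to the full protocol, so its absence is not a fault in itself. It only explains why a reader cannot resolve the contradictions.

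Finally, it would be too strong to say that a null result could not be interpreted. An estimate with its 95% confidence interval remains informative whatever the planning arithmetic was.

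All of these objections stand. None of them removes the two discrepancies between stated figures.

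**Conclusion.** The statement is wrong as written, in two respects. First, 23 with 15% loss gives 28 per group, or 28 to 30 in total, and neither 21 per group nor 42. This is arithmetic on the article's own numbers and rests on no assumption. Second, the calculation uses one-sided 0.005, while the analysis is set at 0.05 with sidedness unstated.

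The stated 80% power is therefore unsupported, and whether it is missed cannot be decided from the documents. The same paragraph is compatible with a trial short of its target and with one larger than it needs to be. The power figures assume a two-group comparison of means, the 4.9-point difference, about 18 evaluable per group, and an SD back-solved from 23 subjects at 80% power.

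The point must be fixed because a core design figure does not follow from its inputs, not because a loss of power has been demonstrated.

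**What to change.** Replace the sample-size sentences in section 2.1 so that they:

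1. say whether 23 is per group or the total;
2. give the SD used and its source;
3. use one alpha and one sidedness, and state the same pair in section 2.4;
4. apply n/(1 − 0.15) to the evaluable number and carry the result through to the total.

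If 42 is the number to be kept, say so, and report the power, or the difference detectable with 80% power, that about 18 evaluable per group gives at the chosen alpha. That difference is (z_α + z_β) × SD/3: 1.14 SD at one-sided 0.005, 0.83 SD at one-sided 0.05 and 0.93 SD at two-sided 0.05.

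The cost is a text amendment. Keeping 42 needs no extra participants. The drawback is that the restated power may be less favourable than 80%.

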## Abstract

*Background and Objectives:* The motor sequelae after a stroke are frequently persistent and cause a high degree of disability. Cortical ischemic or hemorrhagic strokes affecting the cortico-spinal pathways are known to cause a reduction of cortical excitability in the lesioned area not only for the local connectivity impairment but also due to a contralateral hemisphere inhibitory action. Non-invasive brain stimulation using high frequency repetitive magnetic transcranial stimulation (rTMS) over the lesioned hemisphere and contralateral cortical inhibition using low-frequency rTMS have been shown to increase the excitability of the lesioned hemisphere. Mental representation techniques, neurofeedback, and virtual reality have also been shown to increase cortical excitability and complement conventional rehabilitation. *Materials and Methods:* We aim to carry out a single-blind, randomized, controlled trial aiming to study the efficacy of immersive multimodal Brain–Computer Interfacing-Virtual Reality (BCI-VR) training after bilateral neuromodulation with rTMS on upper limb motor recovery after subacute stroke (>3 months) compared to neuromodulation combined with conventional motor imagery tasks. This study will include 42 subjects in a randomized controlled trial design. The main expected outcomes are changes in the Motricity Index of the Arm (MI), dynamometry of the upper limb, score according to Fugl-Meyer for upper limb (FMA-UE), and changes in the Stroke Impact Scale (SIS). The evaluation will be carried out before the intervention, after each intervention and 15 days after the last session. *Conclusions:* This trial will show the additive value of VR immersive motor imagery as an adjuvant therapy combined with a known effective neuromodulation approach opening new perspectives for clinical rehabilitation protocols.

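### The stated randomization list has 30 entries, but the trial plans 42 patients, so the list is 12 entries short and cannot deliver 21 per group.

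*Protocol article*

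**What the plan says.** The abstract gives the total: "This study will include 42 subjects in a randomized controlled trial design". The sample-size paragraph of section 2.1 gives the split, after an allowance for losses: "it will be necessary to reach a sample of 21 patients in each group". The same section says that "patients are randomly assigned to two groups".

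The randomization paragraph of section 2.1 then describes how the allocation is produced. The coding is "A code consisting of two digits (1 and 2) will be used", and the sequence is described as follows: "The application offers a random list of 30 numbers with digits 1 and 2". A remote researcher with no other part in the study generates it, a different staff member assigns patients, and concealment works like this: "The allocation concealment will be made with closed, sealed, and sequentially numbered envelopes".

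The article mentions no second list, extension rule, block size, stratification factor or fixed count of each digit.

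**The concern.** Sequentially numbered envelopes prepared from a 30-entry list end at patient 30. Patients 31 to 42 would have no allocation prepared in advance. Someone would have to decide mid-trial how to continue, or recruitment would stop at 30.

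An allocation fixed and concealed before the first patient enters is the main protection against selection bias. It matters here because one arm attends virtual-reality sessions and the other does not, so staff who deliver treatment can see who is in which arm. Entries added late, after 30 assignments are known, are harder to defend than entries made at the start. Stopping at 30 would instead leave the trial well below the size it says it needs.

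**Working it through.** **Inputs.** List length 30 (section 2.1, randomization paragraph). Total sample 42 (abstract). Sample per group 21, and 23 subjects with 15% loss (section 2.1, sample-size paragraph).

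**Step 1: is 42 the consistent total?** 2 × 21 = 42. The abstract and section 2.1 agree.

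**Step 2: list against sample.** 42 − 30 = 12 entries missing, and 12 / 42 = 28.6%.

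**Step 3: what 30 entries can give.** If the list is balanced, 30 / 2 = 15 per group. If it is not, the smaller group has fewer than 15. In a comparison of two means with equal arms, information is proportional to the total number, so 15:15 carries 30 / 42 = 71% of the information of 21:21. The standard error is larger by a factor of √(42 / 30) = 1.18.

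**Step 4: does another reading of the sample size explain 30?**

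| Reading of 23 | Divide by 0.85 | Multiply by 1.15 |
|---|---|---|
| Total | 27.06, rounded up to 28 | 26.45, rounded up to 27 |
| Per group | 28 per group, 56 in total (55 if 46 is inflated once) | 27 per group, 54 in total (53 if 46 is inflated once) |

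None of these gives 30, and none gives 42. A total of 27 or 28 is near 30 but does not match the planned 42. That 21 per group does not follow from 23 and 15% is a separate problem. It matters here only because the list must cover whatever sample size is finally adopted.

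**Step 5: balance, conditional only.** If 42 digits were drawn independently with probability one half each, the chance of exactly 21:21 would be C(42, 21) / 2^42 = 0.122. The chance that the arms differ by 10 or more would be 0.164. These figures need unrestricted draws, which the article does not state.

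**The case against.** The strongest reply is that this is one inconsistent number in a condensed article. The sequence is generated remotely by someone outside the other procedures, a second person assigns, and the envelopes are sealed. If the same researcher drew a further list in the same way, concealment would hold. That is fair. The article does not show that any patient would in fact be allocated without concealment; it shows only that the stated list does not reach them. What remains is that the figure given for the sequence contradicts the planned sample, and nothing in the text resolves it.

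Three stronger readings are tempting, and the document does not support them.

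- *The arms will probably be unequal because there is no blocking.* The article is silent on restriction, and an article may leave block details to the full protocol. The 12% figure is therefore conditional. Modest inequality also costs little: relative efficiency is 4·n1·n2 / N², so 17:25 keeps 1700 / 1764 = 96% and 16:26 keeps 1664 / 1764 = 94% of the information of 21:21.
- *The list should have been stratified by time since stroke.* The Introduction does say that "improvement is noticeably reduced over the second month, finding stabilization around the sixth month", and eligibility opens after three months. But section 2.1 already excludes the first three months on account of spontaneous recovery, and the Introduction names other prognostic factors too. Stratification is a design preference and not part of this error.
- *This is an open-label trial, so an extension would be biased.* The abstract and section 2.1 call the trial single-blind, and evaluators are kept unaware of group. The Introduction says double-blind, but no section says open-label.

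**Conclusion.** The point holds as a direct contradiction. The stated list has 30 entries for 42 planned patients, a shortfall of 12 (29%). Used alone, it gives at most 15 in the smaller group against 21 planned. This conclusion rests only on the three stated figures 30, 42 and 21. It needs no assumption about the standard deviation, the dropout rate or the way the digits are drawn.

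Whether selection bias or imbalance would follow depends on how the gap is filled and whether the list is restricted, and the article says neither. The correction should be made before the first patient is enrolled, because a gap found after envelope 30 cannot be closed as cleanly.

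**What to change.** Before first enrolment, the independent remote researcher should generate one concealed 1:1 list for the whole final sample. Under the current plan that means at least 42 entries, with 21 of each code. If the sample-size paragraph is corrected to another number, the list should follow it.

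The protocol should state the ratio and that a restriction is used which delivers the planned group sizes. A random ordering of 21 ones and 21 twos does this. Permuted blocks also keep the arms close during recruitment, but small blocks make some assignments guessable when treating staff can see who receives virtual reality. If blocks are used, their sizes should vary and be withheld from recruiting staff.

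All envelopes should be prepared from that one list, and the figures in the abstract and both paragraphs of section 2.1 brought into agreement. If the investigators choose to stratify, each stratum needs its own series with spare entries, since stratum sizes are not known in advance.

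The cost is a few minutes to regenerate the list, 12 more envelopes and a one-paragraph amendment.
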